### Data analysis

Data will be transferred from Case Report Forms to Microsoft® Excel for Windows (current version) spread sheets and later processed by SPSS® (current version). Biomechanical data will be processed with the outlined software and final quantities will also be transferred to spreadsheets for statistical analysis.

Statistical analysis will be performed descriptively after plausibility control. First, testing of normal distribution (Shapiro-Wilk test) of data will be followed by the calculation of mean, standard deviation and 95 % confidence interval. Primary outcome measure (FFI total score) at measurement points 0, week 6 and week 12 will be analysed by 3x3 Analysis of Variance (ANOVA) with repeated measures identifying differences in the FFI across groups (FOO, FOE, FOS) and test sessions. This also applies for the secondary outcome measures (FFI pain subcategory, FFI disability subcategory and FFI activity limitation subcategory). The primary endpoint will be set at 12 weeks. Biomechanical data will be analysed descriptively. Pre-post comparisons of those tertiary outcome measures will also be performed where indicated after descriptive analysis by 2×2 repeated measures ANOVA (factor group and test day).

Sample size calculation has been based on the outlined protocol with three intervention groups and the same primary outcome as Kulig et al. [14, 15], where a sample size of *n* = 15 per group (total *N* = 45) was determined based on clinical observation, attrition rate and power analysis. Clinical observation suggested that there is moderate to high inter-subject variability with respect to pain, disability and function (patient’s perception). A drop-out rate of 20 % is assumed due to a long intervention period, increase or resolution of symptoms during the intervention, or a need for surgery requiring exit from the study. Power analysis was based on an alpha level of 0.05 and beta of 0.8 resulting in the proposed sample size of 45 [38].

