Based on this reported sample size with the same main outcome and design, an *à priori* calculation of the total sample size was performed leading to a group sample of *n* = 20 (total *N* = 60) according to the following assumptions (Software: G*Power3, [68, 69]: test family = F-tests, statistical test = repeated measures ANOVA, effect size = 0.2 (medium), alpha = 0.05, power = 0.82, number of groups = 3, number of measurements = 3, correlation among the repeated measures = 0.5, nonsphericity correction epsilon = 1 and dropouts *n* = 6).

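### The power of 0.82 quoted for a medium effect is power for a 12-week gap of about 0.9 to 1.2 SD between the best and worst arm

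*Protocol article*

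**What the plan says.** All references are to the protocol article, Data analysis.

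- The primary outcome, the FFI total score, is measured at baseline, week 6 and week 12. It is to be analysed by a 3x3 repeated measures ANOVA with factors group and session. The time point of interest is fixed: "The primary endpoint will be set at 12 weeks".
- The calculation is described as "test family = F-tests, statistical test = repeated measures ANOVA", with "effect size = 0.2 (medium), alpha = 0.05, power = 0.82, number of groups = 3, number of measurements = 3" and "correlation among the repeated measures = 0.5, nonsphericity correction epsilon = 1 and dropouts" of 6. The result is 20 per group, 60 in total.
- The paragraph does not say whether the powered effect is the group main effect, the session main effect or their interaction. It gives no FFI difference and no FFI standard deviation.

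**The concern.** In a repeated measures calculation, f = 0.2 has no fixed clinical size. The noncentrality depends on which effect is tested, on the number of visits and on their correlation. A value that looks modest can therefore stand for a large difference between arms at a single visit. The article labels it medium without naming the effect.

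Readers will take 60 participants as giving more than 80% power to detect a moderate benefit of one regimen over another. If that is not so, a non-significant result could be over-read as evidence against a moderate benefit. That would matter here because one arm is a sham orthosis and the Discussion expects clinical implications from the result.

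**Working it through.** **Inputs from the article.** f = 0.2, alpha = 0.05, k = 3 groups, m = 3 measurements, rho = 0.5, epsilon = 1, N = 60 with 6 dropouts. This leaves 54 analysed, 18 per arm.

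**Step 1: reproduce 0.82.** Power from the noncentral F distribution at N = 54:

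| Effect | Noncentrality | df | Power |
|---|---|---|---|
| Group-by-time interaction | f²Nm/(1 − rho) = 0.04 × 54 × 3/0.5 = 12.96 | 4, 102 | 0.816 |
| Session main effect | 12.96 | 2, 102 | 0.898 |
| Group main effect | f²Nm/(1 + (m − 1)rho) = 0.04 × 54 × 3/2 = 3.24 | 2, 51 | 0.327 |
| Interaction, alternative effect-size definition | f²N(m − 1) = 0.04 × 54 × 2 = 4.32 | 4, 102 | 0.330 |

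Only the first row gives 0.82. The smallest balanced N that reaches 0.80 for that row is 54 (N = 51 gives 0.789), and 54 + 6 = 60. Both stated figures are recovered.

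**Step 2: convert interaction f = 0.2 to a 12-week gap.** The article gives no pattern of means, so these are assumptions: equal baselines, a common SD of 1 at each visit, and a week-6 effect between zero and the full week-12 effect. If the largest gap at week 12 is d, the interaction f equals d × SD(arm pattern) × SD(time pattern), where each SD is taken over three values with divisor 3.

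- Arm patterns: one arm differs from two equal arms, or both active arms differ equally from sham (SD 0.471); evenly spread arms (SD 0.408).
- Time patterns over the three visits: linear 0, 0.5, 1 (SD 0.408); all late 0, 0, 1 or all early 0, 1, 1 (SD 0.471).

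Setting f = 0.2 and solving for d gives the third column. The f at week 12 is d × SD(arm pattern). The one-way power at week 12 uses noncentrality 54 × f² with df 2 and 51.

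| Arms | Time | Gap d at week 12 | f at week 12 | One-way power at week 12 |
|---|---|---|---|---|
| One differs | late or early | 0.2/0.222 = 0.90 | 0.42 | 0.78 |
| One differs | linear | 0.2/0.192 = 1.04 | 0.49 | 0.89 |
| Spread | late or early | 0.2/0.192 = 1.04 | 0.42 | 0.78 |
| Spread | linear | 0.2/0.167 = 1.20 | 0.49 | 0.89 |

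So f = 0.2 on the interaction scale is more than twice that value at the 12-week visit.

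**Step 3: power of the interaction test at a moderate gap.** The article does not define medium as a difference, so 0.5 SD is an assumption. The noncentrality is 54 × 6 × f² = 324 f², with df 4 and 102.

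- Spread, linear: f = 0.5 × 0.1667 = 0.0833, noncentrality 2.25, power 0.18.
- One differs linear, or spread late or early: f = 0.0962, noncentrality 3.00, power 0.23.
- One differs, late or early: f = 0.1111, noncentrality 4.00, power 0.31.

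As a range check, at a gap of 0.8 SD the noncentralities are multiplied by (0.8/0.5)² = 2.56, to 5.76, 7.68 and 10.24. The powers are then 0.43, 0.56 and 0.71, still short of 0.82.

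**Step 4: pairwise detectable differences, for context.** Two-sided noncentral t, 18 per arm. Residual variance is 1 − 0.5² = 0.75 with baseline adjustment (33 df) and 2(1 − 0.5) = 1 on change scores (34 df).

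| Analysis | Gap for 80% power, alpha 0.05 | Gap for 80% power, Bonferroni for three pairs |
|---|---|---|
| Baseline-adjusted | 0.83 SD | 0.98 SD |
| Change scores | 0.96 SD | 1.13 SD |

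**The case against.** The strongest defence is that nothing has been miscalculated. Both 0.82 and 54 + 6 = 60 reproduce. The effect that reproduces them belongs to the planned 3x3 ANOVA and is the natural treatment term when baseline is one of the sessions. That stands. So does the point that a condensed article may leave out the software sub-option, since a reader can recover it from the inputs.

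A reader might go further and infer that the 12-week comparison of arms is weaker than the test that was powered. The document does not support that. At the 0.9 to 1.2 SD gap which the calculation implies, the one-way comparison at week 12 has power of 0.78 to 0.89. Nor is it fair to carry f = 0.2 unchanged to a one-way test at week 12 and report its low power as the trial's power, because that mixes two effect-size scales. The group main effect figure of 0.327 likewise concerns a comparison averaged over sessions that include baseline. It serves here only to identify which effect was powered.

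It is also true that 0.5 SD is not a target the article sets, and that the article plans no equivalence claim or rule for reading a null result.

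The label remains. It is printed beside the power figure, and no later analysis plan can make a 0.9 to 1.2 SD gap a medium one.

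**Conclusion.** The point holds as a mislabelled effect size. The stated power of 0.82 is correct for the group-by-time interaction at f = 0.2, but that f stands for a large difference at week 12, about 0.9 to 1.2 SD between the best and worst arm. At a moderate gap of 0.5 SD the interaction test has power of 0.18 to 0.31, so a true gap of that size would be missed in roughly 70 to 80% of such trials.

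The conclusion rests on four things: the identification of the interaction, which is inferred from the match on both N and power because the article does not name it; equal baselines; the article's own correlation of 0.5 and epsilon of 1; and a week-6 effect no larger than the week-12 effect and in the same direction. Because no FFI standard deviation is given, the sizes cannot be turned into FFI points.

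**What to change.** Keep N = 60 and the planned analysis, and reword the sample size paragraph:

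1. Delete the word medium.
2. State that 0.82 is the power of the group-by-time interaction at f = 0.2 (within-between scale of the software) with 54 completers.
3. State that, with equal baselines, this corresponds to a gap of about 0.9 to 1.2 SD between the best and worst arm at week 12, depending on the pattern of arms and the timing of the effect.
4. State that power for a 0.5 SD gap is about 0.2 to 0.3.
5. If a pairwise detectable difference is also given, name the analysis and the multiplicity rule beside it, using the matching entry in the Step 4 table. The 0.83 SD figure should not stand alone, because the article plans no baseline-adjusted pairwise test and three arms give three pairs.

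The cost is wording only. The stated sensitivity becomes less favourable; recruitment, endpoint and conduct do not change.

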## Discussion

The objective of this randomised trial is the evaluation of the therapeutic benefit of three different non-surgical treatment regimens (foot orthoses only FOO, foot orthoses and eccentric exercise FOE, sham foot orthoses FOS) in patients with pes planovalgus and accompanying complaints. The clinical validity of those therapy regimens will result in important clinical implications.

The lack of evidence for non-surgical treatment strategies emphasises the need for such a trial. Beside the fact that established clinical outcomes will be used to assess clinical efficacy of therapy regimens, the novel aspect of the trial is to integrate biomechanical measurements of lower extremity and foot function.

The development and final set-up of the intervention groups was the subject of great debate between the investigators, the funding agency’s international reviewers and the ethics committee. The author/investigator group initially planned foot orthoses as the basic therapy for all three groups. The promising results of the aforementioned RCT by Kulig et al. [15] justified this approach [38]. Consequently, according to the best available evidence, foot orthoses were planned for all groups. One group with additional eccentric exercises and one group with additional “traditional” physiotherapy (a regimen of ice, ultrasound, electrotherapy, manual therapy) were planned to assess the additive effect of exercise therapy and physiotherapy. The rationale for eccentric exercises was derived from existing evidence for the treatment of (chronic) tendinopathy [51, 50, 52]. Physiotherapy was planned to be integrated into this trial because it reflects current physiotherapeutic practice in the daily routine. The reviewers of the funding agency rejected the physiotherapy therapy modality due to lack of any scientific evidence. During the process of ethics approval, the regional ethics committee, acting as the legal authority in Switzerland came to the conclusion that there is also no rationale for foot orthoses since the trial by Kulig et al. did not evaluate foot orthoses against a wait-and-see approach [15]. They concluded that research ethics allow refraining from foot orthoses in this patient group. Consequently, they requested an untreated control group. The investigator group emphasised that there are frequent dropouts in such a control group and suggested a sham orthosis group as a control. The ethics committee finally approved this idea and the funding agency also accepted the final therapy group definitions.

The rationale for the measurement of the gait mechanics and neuromuscular control in this trial is to gain a comprehensive view on functional changes due to pathology and their plasticity during the intervention. One study has analysed kinematic differences between healthy and PTTD patients in a heel rise movement [70]. It found that stage II PTTD patients exhibited greater plantar flexion to achieve heel rise compared to healthy controls [70]. The same study found greater tibialis posterior muscle lengthening during walking and greater hindfoot eversion during stance [71, 72].

The tibialis posterior muscle is the main muscular stabiliser for active longitudinal arch stabilisation [73]. Foot orthoses with an arch support have been found to selectively activate the tibialis posterior muscle [74]. Therefore, it would be the best muscular indicator in the context of pes planovalgus, but measurements of this deep lower leg muscle are not possible with surface electromyography. Accordingly, the trial refrains from using highly invasive techniques, so as to not place study participants at risk. There are reports of synergistic activity of the tibialis posterior muscle and the superficially available peroneus longus muscle [29]. The approach is, therefore, to evaluate easily available parameters that can be transferred to clinical settings. Further assessment of the tibialis anterior muscle and gastrocnemius (medialis and lateralis) muscles [66, 34, 33, 35] will be performed to cover the “neuromuscular” dimension that relate to common kinematic movements like dynamic navicular drop, rearfoot eversion, etc.

The analysis of possible functional changes in gait mechanics and neuromuscular control will contribute to an enhanced understanding of functional changes that occur with conservative management. This will enable us to generate theories about the mechanisms possibly involved in the process of symptom relief. Furthermore, a subsequent aim is to optimise conservative management strategies, which may lead to more efficient use of health care resources.
